## Results

The study received internal funding support from the University of Melbourne in September 2024. MRI paradigm development and testing with 5 healthy volunteers commenced in September 2024 and was finalized in July 2025. Participant recruitment began in July 2025, and data collection commenced in August 2025 and was concluded by mid-2026. As of September 2026, 13 participants have been recruited, and data will be analyzed by the end of 2026, with results expected to be published in 2027.

## Discussion

### Principal Findings

Music therapy has demonstrated feasibility and effectiveness in reducing negative symptoms and/or enhancing quality of life in a range of chronic mental health and physical health conditions. This study outlines a unique protocol for a mixed methods pre-post pilot test that is based on findings from 3 prior case studies using the same intervention, which resulted in improved outcomes among all participants. It aims to investigate whether music therapy reduces anhedonia symptomatology and to explore the interaction between a combination of biophysiological, neuropsychological, and sociobehavioral mechanisms of improvement. Biophysiological mechanisms will be investigated through a comparison of musical pleasure in healthy volunteers and the intervention group. Neuropsychological mechanisms will be investigated using a comparison of preintervention and postintervention test scores on psychometric measures of anhedonia. Sociobehavioral outcomes will be explored through evaluative interviews that probe the importance of the regular therapeutic care and support provided.

No other studies have integrated data to explore the effect of music therapy on anhedonia. Only 1 other study has been identified that reports improvements in anhedonia symptoms, which was based on a similar program that used mindfulness as the key intervention rather than music therapy [8]. We hypothesize that musical pleasure may serve as a gateway to the reactivation of the pleasure system and propose that regular, guided, personally selected pleasure-inducing music activities can promote increased limbic activity, which may be one mechanism through which music therapy reduces anhedonia symptomatology. Currently, this is a 4-month process involving weekly meetings with the guiding therapist and daily engagement with pleasure-inducing music-based activities. This process could be changed and/or made more efficient with different populations once the mechanism is better understood.

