### Study Design

Given the findings from previous case studies, a sequential mixed methods study design is suitable for use in this pre-post pilot study to explore congruences between psychometric, interview, and fMRI data regarding changes in hedonic capacity among individuals with anhedonia following the music therapy intervention. Neither a strictly explanatory nor exploratory model (according to Creswell and Plano [44] definitions) is used, but the design will prioritize quantitative data from psychometric scales and seek to understand any significant differences from before to after intervention using interview data collected after intervention. This will cautiously extend case study findings of the same music therapy intervention [21,22] to determine whether psychometric outcomes are significant at the group level, as well as to explore patterns in the interview data to better understand any changes on the 2 different outcome measures—the DARS [45] and the Snaith-Hamilton Pleasure Scale (SHAPS) [46]. It would be premature to include a control condition at this stage, and similarly, the sampling of participants will be restricted to high-functioning people with anhedonia to better understand the phenomenon before extending the research to more clinical populations, such as those with schizophrenia or MDD. In addition, the study will assess the feasibility of the intervention and study procedure to inform a subsequent larger-scale study [47]. Feasibility measures will evaluate the acceptability, adherence, and practicality of delivering the intervention in adults with high cognitive function, while preliminary estimates of intervention effects and variability will be used to inform sample size calculations and the design of a future fully powered study.

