### Eligibility Criteria

To identify participants with anhedonia, communications included a link to an online screening survey that prospective participants could independently access, comprising the DARS and questions assessing the inclusion criteria. The research team reviewed all survey responses, and eligible prospective participants were identified as scoring <44 on the DARS [45], based on the group differences identified between patients with major depressive episodes and healthy controls. This score has also been used in a study of university students where none of the healthy controls scored <44 points on the total scale [52]. All participants were required to complete a magnetic resonance imaging (MRI) safety implant checklist and be screened by qualified radiographers to deem them compatible with an MRI scan.

The inclusion criteria are being a professional, research, or academic member of the university community, having the cognitive capacity to select and discuss pleasure-inducing music, being aged >18 years, scoring <44 on DARS, agreeing to participate and having the capacity to provide informed consent, having a self-identified interest in music, and having English literacy skills suitable for participation in interviews. Exclusion criteria for all groups are failure to meet scanning requirements, including having metallic objects in the body (eg, a cardiac pacemaker or cochlear implant), a history of claustrophobia, permanent metal dental appliances, or a body weight ≥120 kg, or having a diagnosis of schizophrenia or MDD.

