### Limitations

The lack of a control group and the small sample size are limitations of the study design. A control group will be included in subsequent studies, once we have determined whether the intervention increases hedonic capacity among individuals with anhedonia and whether any congruences across psychometric results and interview data are identified. This pilot will also enable us to test whether the musical pleasure fMRI paradigm can produce results indicative of reward pathways in those with anhedonia. Nevertheless, it will remain challenging to blind both participants and researchers. The enhanced sensitivity and specificity of fMRI data acquired on the 7T MAGNETOM Plus MRI system may help mitigate the limitations associated with the small number of participants.

There will be some flexibility in the delivery of the intervention since therapeutic integrity is challenged by an overly fixed intervention manual that does not respond to presenting needs. We have published the music therapy intervention [22] that addresses validity and replicability by transparently outlining four categories of principles: (1) unique and essential, (2) essential but not unique, (3) acceptable but not necessary, and (4) not acceptable (proscribed), as recommended in previous music therapy studies [59]. This framework has been used in this study and in additional case studies.

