### Conclusions

It is hoped that the results of this pilot study will contribute to an understanding of the benefits of music therapy for people with anhedonia, as well as whether musical pleasure mediates outcomes of music therapy more broadly, particularly in chronic mental and physical health conditions. Greater knowledge of both of these possibilities could result in improved quality of life for people living with chronic ill health, particularly for those with anhedonia, which is associated with poorer treatment adherence and worse long-term outcomes [60] and for which few helpful interventions have been identified to date. This could lead to further exploration and understanding of the role of creative arts therapies and leisure activities in supporting people living with chronic conditions more broadly.

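### The Discussion promises a healthy-volunteer comparison for the biophysiological mechanism, but no section of the plan defines a healthy group or a between-group analysis

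*Protocol article*

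**What the plan says.** The Principal Findings part of the Discussion names three kinds of mechanism of improvement and gives each a source of evidence. For the first it says: "Biophysiological mechanisms will be investigated through a comparison of musical pleasure in healthy volunteers and the intervention group". The statement is in the future tense and is the only route that this paragraph gives for the biophysiological strand.

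The sections that define the study describe a single group:

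- **Objectives.** RQ 1 is feasibility. RQ 2 sets psychometric change beside interview accounts. RQ 3 asks whether pre-post change in reward-region activity goes with change in anhedonia symptoms.
- **Eligibility Criteria.** The screening rule is that "eligible prospective participants were identified as scoring <44 on the DARS". The exclusion criteria are introduced in the plural, as applying to all groups, but only one group is described.
- **Sample Size.** The number is 13, with none given for healthy volunteers.
- **Data Analysis.** The music-task contrast is pleasurable against neutral music within a person. The group-level model crosses that contrast with time, both as within-subject factors.

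Healthy volunteers who belong to this study appear in one other place, the Results section: "MRI paradigm development and testing with 5 healthy volunteers commenced in September 2024 and was finalized in July 2025". The same section continues: "Participant recruitment began in July 2025, and data collection commenced in August 2025 and was concluded by mid-2026". The healthy controls mentioned in the Background and in Eligibility Criteria come from cited studies.

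**The concern.** The article commits to a specific comparison that its own design and analysis sections do not contain. A reader cannot tell which analysis is meant to address the biophysiological question: the between-group comparison in the Discussion or the within-person model in Data Analysis.

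Two things are at stake. First, if the results paper sets the 13 participants against the 5 development volunteers, a difference could reflect who was scanned, when, or on which version of the task, and yet be reported as mechanism. Second, even a clean difference between healthy people and people with anhedonia describes a state. The Discussion presents these strands as mechanisms of improvement, which is a statement about change.

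**Working it through.** The article states no figure for this comparison, so there is nothing to reproduce. The check sets the sections side by side and then asks what the comparison could show.

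**Step 1. Is there a healthy group or a between-group analysis anywhere?**

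| Section | What it provides | Healthy group or group factor? |
|---|---|---|
| Objectives, RQ 1 to 3 | Feasibility; pre-post change | No |
| Eligibility Criteria | DARS below 44 for everyone enrolled | No; plural wording, but no second group defined |
| Outcomes, Participant Timeline | Measures and visits of intervention participants | No |
| Sample Size | 13 | No |
| Data Analysis | Contrast by time, within subject | No |
| Results | 5 volunteers for paradigm work | Not named as a comparator |
| Discussion, Principal Findings | Healthy volunteers against intervention group | Yes, the only place |

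**Step 2. If the 5 volunteers are the comparator, what differs besides group?**

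- Period: September 2024 to July 2025 for the volunteers, August 2025 to mid-2026 for the participants. On these dates the two periods do not overlap.
- Task version: the paradigm was under development until July 2025. The article does not say which tasks the volunteers did or whether any were scanned on the final version, so this difference is possible but not established.
- Selection: no eligibility criteria, DARS range or matching is stated for the volunteers.

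**Step 3. Could the comparison show a mechanism of improvement?** Let H be the volunteers' mean pleasurable-minus-neutral response, and A0 and A1 the participants' means before and after the intervention. Assume that each volunteer contributes one measurement; the article describes no repeat.

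- Comparison before the intervention: H − A0. This mixes anhedonia status with everything in Step 2 and contains no change.
- Comparison after the intervention: H − A1. The same holds.
- Difference between the two: (H − A0) − (H − A1) = A1 − A0.

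The healthy mean cancels. What remains is the within-participant change that Data Analysis already plans to estimate. RQ 3 then relates change in activity to change in symptoms, and H does not enter that association either. The healthy group may help to describe where participants start, but it adds nothing to the estimate of change.

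**The case against.** The strongest reply is that this is one sentence in a Discussion. The comparison is not a research question and no planned analysis depends on it. A condensed article may also leave a reference group to the full protocol, and the plural in the exclusion criteria hints that one may exist. Part of this stands: the article does not prove that no healthy group exists anywhere. But the point does not rest on missing detail. The article makes a positive statement that its own sample size and group-level model do not accommodate, and Step 3 applies however well a healthy group measured once is defined.

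Some stronger readings are tempting and should not be drawn:

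- A reader might infer a direct contradiction from "It would be premature to include a control condition at this stage" and "The lack of a control group and the small sample size are limitations of the study design". In context both most naturally mean a comparator for the intervention; the Limitations go on to say "A control group will be included in subsequent studies, once we have determined whether the intervention increases hedonic capacity among individuals with anhedonia". A healthy reference group is compatible with these statements, so they are not evidence here.
- A reader might take it as fact that the 5 volunteers are the comparator and were scanned on a superseded task. The article says neither.
- A reader might calculate power for 5 against 13. No such test is planned, Sample Size already concedes that the study is underpowered for inference, and Data Analysis reports the P values for the two scales descriptively only.
- A reader might conclude that the biophysiological question is lost. It is not: RQ 3 and the planned contrast give an exploratory within-person route.
- A reader might object to the hope in the Conclusions of learning "whether musical pleasure mediates outcomes of music therapy more broadly". That is an aspiration, and no mediation analysis is claimed.

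**Conclusion.** The point holds as an inconsistency between one Discussion sentence and the sections that define the study. The biophysiological strand, one of three, is tied to a comparison for which the article defines no group, number or analysis. If the 5 development volunteers are meant, group is confounded with scan period, and with task version to an unknown degree. A cross-sectional difference would not show a mechanism of change in either case.

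No numerical size attaches to this. The consequence is for what the trial may conclude about mechanism; the primary feasibility aim and the planned pre-post analyses are unaffected. The conclusion assumes that the article's eligibility, sample size and analysis sections represent the study, that the volunteers' data come from the development period given in Results, and that musical pleasure in the quoted sentence refers to the music-task response.

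**What to change.** Replace the sentence in Principal Findings with a statement that the biophysiological question is explored through the planned within-participant, pre-post change in the pleasurable-minus-neutral music contrast and its association with symptom change, as in RQ 3.

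If any healthy-volunteer scans are shown, limit them to those run on the final paradigm and present them descriptively as a check that the paradigm works, with no group test and no conclusion about mechanism. If the full protocol does define a healthy group, the article should state its source, criteria, number, tasks and timing and label the comparison descriptive. The plural in the exclusion criteria should be brought into line either way.

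The cost is a reworded sentence, one adjusted phrase and the loss of one claimed comparison. No new data are needed. Analysis is due to finish by the end of 2026, so the wording can be settled before results are reported.

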### Limitations

The lack of a control group and the small sample size are limitations of the study design. A control group will be included in subsequent studies, once we have determined whether the intervention increases hedonic capacity among individuals with anhedonia and whether any congruences across psychometric results and interview data are identified. This pilot will also enable us to test whether the musical pleasure fMRI paradigm can produce results indicative of reward pathways in those with anhedonia. Nevertheless, it will remain challenging to blind both participants and researchers. The enhanced sensitivity and specificity of fMRI data acquired on the 7T MAGNETOM Plus MRI system may help mitigate the limitations associated with the small number of participants.

There will be some flexibility in the delivery of the intervention since therapeutic integrity is challenged by an overly fixed intervention manual that does not respond to presenting needs. We have published the music therapy intervention [22] that addresses validity and replicability by transparently outlining four categories of principles: (1) unique and essential, (2) essential but not unique, (3) acceptable but not necessary, and (4) not acceptable (proscribed), as recommended in previous music therapy studies [59]. This framework has been used in this study and in additional case studies.

### Conclusions

It is hoped that the results of this pilot study will contribute to an understanding of the benefits of music therapy for people with anhedonia, as well as whether musical pleasure mediates outcomes of music therapy more broadly, particularly in chronic mental and physical health conditions. Greater knowledge of both of these possibilities could result in improved quality of life for people living with chronic ill health, particularly for those with anhedonia, which is associated with poorer treatment adherence and worse long-term outcomes [60] and for which few helpful interventions have been identified to date. This could lead to further exploration and understanding of the role of creative arts therapies and leisure activities in supporting people living with chronic conditions more broadly.
